### Assessment of therapists’ awareness of negative change

In order to evaluate therapists’ awareness of patient negative change, the congruence between therapist and patient estimates of outcome is calculated, when the patient is NOT. Therefore, therapist rated outcome will be assessed at each session via the Global Assessment of Functioning Scale (GAF; [41]). In accordance with the truth and bias model, congruence is defined as the correlation between the therapists’ assessments of patients’ global functioning (measured with the GAF) and patients’ assessment of their functioning (measured with the HSCL) [42, 43]. In this sense, the more similar therapists’ change ratings are in relation to patients’ change ratings, the better is the awareness of the therapists concerning the negative change of this specific patient.

### Assessment of control variables

Treatment integrity will be assessed as adherence and competence. Competence will be evaluated with the Cognitive Therapy Scale (CTS; [44, 45]) and adherence with the Cognitive-Behavioral Therapy Adherence Scale (CBT-AS; [46]). All sessions are videotaped. Three master-level independent raters will evaluate a random selection of 10% of all sessions per treatment to assess the quality of cognitive therapy. All raters will be trained in an 18-h training prior to the evaluation and will be blinded concerning treatment outcome and treatment condition. Also interrater reliability will be ensured in the training procedure. To check for the use and influence of non-psychometric feedback on the effects of psychometric feedback the item 8^2^ in the CTS scale will be used as a control variable (using feedback and summaries).

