**Methods/design:**

The research project investigates in a randomized controlled trial the effectiveness as well as moderating and mediating factors of psychometric feedback to therapists. In the intended study a total of 423 patients, who applied for a cognitive-behavioral therapy at the psychotherapy clinic of the University Trier and suffer from a depressive and/or an anxiety disorder (SCID interviews), will be included. The patients will be randomly assigned either to one therapist as well as to one of two intervention groups (CG, IG2). An additional intervention group (IG1) will be generated from an existing archival data set via propensity score matching. Patients of the control group (CG; *n* = 85) will be monitored concerning psychological impairment but therapists will not be provided with any feedback about the patients assessments. In both intervention groups (IG1: *n* = 169; IG2: *n* = 169) the therapists are provided with feedback about the patients self-evaluation in a computerized feedback portal. Therapists of the IG2 will additionally be provided with clinical support tools, which will be developed in this project, on the basis of existing systems. Therapists will also be provided with a personalized treatment recommendation based on similar patients (Nearest Neighbors) at the beginning of treatment. Besides the general effectiveness of feedback and the clinical support tools for negatively developing patients, further mediating and moderating variables on this feedback effect should be examined: treatment length, frequency of feedback use, therapist effects, therapist’s experience, attitude towards feedback as well as congruence of therapist’s and patient’s evaluation concerning the progress. Additional procedures will be implemented to assess treatment adherence as well as the reliability of diagnosis and to include it into the analyses.

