Three moderators and two mediators of the feedback effect will be investigated in hypotheses 3 and 4 (see also Fig. 1): Moderators: therapists’ attitudes towards feedback, feedback usage and diagnoses; Mediators: Therapists’ awareness for negative developments and treatment length. In order to control for therapist effects, therapists will be modelled as random effects at level two.

Therefore, *Optimal Design Software for Multilevel and Longitudinal Research* (Version 3.01; [50]) was used to determine the minimal effect that can be detected with sufficient power, given the sample size calculation above. Assuming a therapist effect of 5% and k = 50 therapists delivering the treatments to j = 8 patients each, a small effect (d = .2) can be detected with sufficient power (1-β = .8). Thus, given the sample size calculated for the primary hypotheses, the secondary analyses can be conducted with sufficient power using multi-level models (e.g., [51]). Ensuring the stability of the results, all analyses will be checked with Mplus software (e.g., [52]).

Additional Monte Carlo simulations with Mplus (Version 7; [52]) were run to specifically test the mediation models from hypotheses 3 and 4. Assuming again small effects for the direct associations, 10,000 datasets have been simulated with the actual sample size of the study sample. These simulations revealed a sufficient power of 1-β = .874. Thus, given the sample size calculated for the primary hypotheses, the mediation analyses can also be conducted with sufficient statistical power to detect indirect mediation effects adjusting for above described control variables.

Furthermore, the analyses will be controlled for the following potential influencing factors: comorbidity (number of additional diagnoses, additional personality disorders), initial impairment, clinical experience as well as experience with the feedback system.

Finally, the data of the project will have a hierarchical data structure because patients will be nested within therapists. Two-level hierarchical models will be applied to the data to correct for therapist influences [51].

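### CTS item 8, rated in session after allocation, is named as a control variable; the mediation models appear to adjust for it, and its place in the H1/H2 models is unclear

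*Protocol article*

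**What the plan says.** Four places in the protocol article bear on this.

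- **Assessment of control variables.** The section opens "Treatment integrity will be assessed as adherence and competence". The source is session video: "Three master-level independent raters will evaluate a random selection of 10% of all sessions per treatment". It then gives item 8 a purpose, "To check for the use and influence of non-psychometric feedback on the effects of psychometric feedback the item 8", and a role: it "will be used as a control variable (using feedback and summaries").
- **Abstract, Methods/design.** "Additional procedures will be implemented to assess treatment adherence as well as the reliability of diagnosis and to include it into the analyses". How adherence is to be included is not said.
- **Sample size calculation and data analyses, mediation power.** The simulations are said to show enough power for "indirect mediation effects adjusting for above described control variables".
- **Same section, next paragraph.** A further list of factors to be controlled for is given: "comorbidity (number of additional diagnoses, additional personality disorders), initial impairment, clinical experience as well as experience with the feedback system". Item 8, adherence and competence are not in it.

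The ANOVAs used to size H1 and H2 name no covariates.

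**The concern.** A rating of therapist behaviour during treatment is not a baseline covariate. The article describes support tools that suggest how to adapt a failing treatment (Background). It also plans to record the changes therapists make because of feedback, as path b of Fig. 1 (Assessment of feedback related variables). If those changes show up in item 8 or the integrity ratings, the ratings lie between group and outcome.

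Two things would follow. In H1 and H2, adjustment would replace the total effect of feedback or tools with the part that does not pass through the rating. In H4, the rating would be a confounder of mediator and outcome that is itself affected by group. Ordinary covariate adjustment then blocks some of the paths the mediation model sets out to measure.

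A main-effect covariate also does not answer the question the article asks of item 8, namely whether ordinary, non-psychometric feedback alters the effect of psychometric feedback. That is a question of contamination or effect modification. It calls for a comparison by group or an interaction term.

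**Working it through.** **Step 1. Which variables does the mediation sentence refer to?** The list of comorbidity, impairment and experience comes after the mediation sentence and is introduced as an addition. It is therefore not what that sentence means by control variables described above. The only earlier section with that label is the one containing item 8, adherence and competence. Reading the sentence as reaching that section is the natural reading, though not the only possible one.

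**Step 2. Which models are affected on the text?**

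| Variable | Called a control variable? | Mediation models | H1/H2 models |
|---|---|---|---|
| CTS item 8 | Yes, explicitly | Yes, by the natural reading | Not stated |
| Adherence, competence | By section heading only; text says assessed | Possibly | Not stated; abstract says adherence is included, not how |
| Comorbidity, initial impairment, clinical and system experience | Yes, in the further list | Yes | Yes (the list says the analyses in general) |

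**Step 3. Reproduce the planned H2 figure.** Inputs from the sample size section: d = .30, so f = d/2 = .15; two groups; m = 2 assessments; correlation .4; alpha .05; power .80. For the group-by-time interaction, with 1 and N - 2 degrees of freedom, lambda = N × m × f² / (1 - rho) = 108 × 2 × .0225 / .6 = 8.1. Power is .805, and 108 is the smallest even N reaching .80. The stated 108 is reproduced.

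**Step 4. What adjustment could do to d = .30.** The shift s (group effect on the rating, in SD) and slope b (rating on outcome, given group) are assumptions; the documents give neither. Without a common cause of rating and outcome, adjusted effect = .30 - s × b.

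| Shift s | Slope b | Adjusted effect |
|---|---|---|
| 0 | any | .30 |
| 0.2 | 0.2 | .30 - .04 = .26 |
| 0.2 | 0.4 | .30 - .08 = .22 |
| 0.4 | 0.2 | .30 - .08 = .22 |
| 0.4 | 0.4 | .30 - .16 = .14 |

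A simulation of 400,000 patients per setting gave .264, .220, .218 and .141 for the four non-zero rows.

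Now add an unmeasured common cause with loading .4 on both rating and outcome. The slope the regression uses becomes b + .4 × .4 = b + .16. The four simulated values then fall to .225, .183, .158 and .076. With no shift, the adjusted effect stays at about .30 even then.

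The sign is not fixed. With s = 0.4 and b = -0.2, the adjusted effect would be .30 + .08 = .38.

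**Step 5. Power at N = 108 if a share p of d = .30 runs through the rating.** Here f = .15 × (1 - p). The table counts only the smaller effect and ignores any gain from reduced residual variance.

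| p (assumed) | Effect | Power at 108 | N needed for .80 |
|---|---|---|---|
| 0 | .30 | .805 | 108 |
| .10 | .27 | .718 | 132 |
| .20 | .24 | .616 | 166 |
| .30 | .21 | .506 | 216 |
| .50 | .15 | .292 | 422 |

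The .26-.14 range in Step 4 corresponds to p of .04/.30 = 13% to .16/.30 = 53%.

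**The case against.** The strongest reply is that this is a label, not a specified model. The H1/H2 ANOVAs carry no covariates, the explicit covariate list is already pre-treatment, and integrity is only said to be assessed. A by-group integrity check would satisfy the abstract. Item 8 is there to separate ordinary in-session feedback from the tested system. The adaptation tools target alliance, motivation, social support, life events and emotion regulation, not CBT adherence or item 8. An article may also leave the covariate set of each model to a fuller document.

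Much of this stands, and it rules out several stronger readings that a reader might infer:

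- **That all three ratings are entered in the H1/H2 models.** The text does not say so.
- **That item 8 measures use of the feedback portal.** It is used for non-psychometric feedback. Portal use is logged separately and is a moderator in H3.
- **That the intervention is designed to change these ratings.** This is an inference from the general aim of adapting treatment, not a stated target.
- **That a randomised comparison is spoiled.** H1 (IG1 against CG) and H2 (IG2 against IG1) both involve the archival, propensity-matched IG1, so neither is a randomised comparison. The accurate term is post-allocation.

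The reply does not dispose of the explicit designation of item 8 as a control variable, or of the mediation sentence that appears to carry it into those models. Leaving the details to another document would excuse silence. Here the article does speak, and it names a variable measured during treatment.

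**Conclusion.** The point holds in limited form. The article commits item 8, a post-allocation rating, to use as a control variable, and by the natural reading adjusts the mediation models for it. Adherence and competence may follow. Entry into the H1/H2 models is unclear.

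The harm depends on allocation shifting the ratings, which is plausible but undocumented. The fall from .30 to about .26-.14 illustrates assumed shifts and slopes of 0.2-0.4 and is not an estimate. It would be wrong to state a fixed percentage loss, or to say that the bias must run against the tools.

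**What to change.** State in the analysis section that the H1, H2 and H4 models adjust only for variables fixed before treatment, namely those in the existing list: comorbidity, initial impairment, clinical experience and experience with the feedback system. Amend the control-variables section and the mediation sentence to agree.

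Report item 8, adherence and competence by group as contamination or integrity checks. Use them in models only in labelled secondary analyses: an interaction with group for the non-psychometric feedback question, a sensitivity analysis, or an additional mediator in H4. The last matters because leaving such a rating out of H4 does not remove confounding of mediator and outcome if the rating affects both.

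The cost is a few sentences. No data collection changes, and the H2 requirement stays at 108 with power .805.

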### Implementation of feedback and clinical adaptation and support tools

Each therapist is able to login after each session to the online feedback portal to get an overview about status and progress of his/her patient in the intervention groups (IG1 & IG2). For patients of the IG1, therapists are provided with information about the initial status concerning symptoms (BSI & OQ-30), interpersonal functioning (IIP-32 & OQ-30) as well as diagnoses specific symptoms (GAD-7 or PHQ-9). Beside the status measures, also individual progress information on the symptom level (HSCL-11 each session) is provided to the therapist (see line with dots in Fig. 3). Higher values indicate more distress. The gray curve represents the expected treatment response for this specific case based on growth curve models developed for the nearest cases (nearest neighbors). Additionally to the expected treatment response (gray curve) a black signal curve beginning from session 5 is displayed (90% confidence boundary). This curve will be recalculated after each session considering the already made progress up to this point. When a patient lies above the black curve (90% confidence boundary), a warning signal is presented within the feedback system.

**Fig. 3 Fig3:**
[figure not shown]
Progress of two different simulated patient examples measured with the HSCL-11. On the left, a negatively developing patient who went off-track during the course of treatment and on the right side a positively developing patient who stays on-track after session 10

**Fig. 4 Fig4:**
[figure not shown]
Personalized strategy recommendations and nearest neighbor therapists

**Fig. 5 Fig5:**
[figure not shown]
Example screenshot from the feedback system in the IG2. All orange signals within the box are linked to respective adaptation and problem solving tools. For therapists in the IG1 neither the signals in the red box nor the access to the tools will be included

Therapists of the IG1 will be able to see status and progress reports as described above (including an overall evaluation of progress in the HSCL, but not expected treatment response and the confidence boundary) whereas the IG2 will get additional access to CSTs implemented in the system. The CSTs are divided into two main areas: a personalized treatment recommendation module and a personalized treatment adaptation module.

### Personalized treatment recommendation

The personalized treatment recommendation is available at the beginning of treatment. The therapists will be provided with important information for their patients on different domains like risk for suicidality, substance abuse, treatment expectation, drop-out risk, symptomatology, and interpersonal functioning.

Additionally, a treatment recommendation for the early phase of treatment is given (Fig. 4). Already treated similar cases within the outpatient center are selected. Therapists rated whether they chose a more problem-solving focused approach, a more motivation-oriented approach or a mixed approach for these cases based on session reports. Based on the closest cases of already treated patients with those three strategies an effect-size is calculated for each of the three interventions. Thus, therapists receive a recommendation which early treatment strategy might lead to the best treatment effect for this particular case. The ten closest cases are depicted in another graph with their treating therapist. This leads to the opportunity that therapists are able to contact therapists who already treated similar cases for peer-supervision.

### Personalized treatment adaptation

To make sure that adaptation and support tools are addressing the right domains in the course of treatment, the Assessment for Signal Clients (ASC) as well as the Affective Style Questionnaire (ASQ) are measured every fifth session (Fig. 5). The four subscales of the ASC are used to measure therapeutic alliance, motivation, social support, and life events. Based on a cut-off value for each measure “orange” (in Fig. 5 light grey) or “green” (in Fig. 5 dark grey) signals are provided for patients who were identified as on risk for treatment failure. The ASQ is used as a marker for the extent of the emotional regulation ability of the patient with the same purpose. If orange signals are detected on one of the five scales (ASQ and/or ASC) then the therapist is able to click on the scale and to open a website with more information on those tools for a specific domain. This additional specific clinical guidelines are oriented on the Clinical Support Tools developed by Lambert et al. and are translated and adapted to the German outpatient setup [5]. Those original tools are extended by using additional clinical as well as video and audio material. Prior to the beginning of the project, participating therapists are instructed and trained on the new feedback portal by the research associate of the project and a video clip, which explains the system.

### Sample size calculation and data analyses

Since the two main hypotheses are based on pairwise comparisons of the NOT patients, the sample size calculation was done so that the size of these comparisons have sufficient power (1-β = .8). Power analyses for the main hypotheses have been conducted with GPower 3.1 [47]. Hypothesis 1 postulates a superior treatment outcome for NOT patients in the IG1 compared to the CG. The average effect for feedback in NOT patients compared to treatment as usual found in the literature is between *r =* .25 [17]. To find this effect in a two-way repeated measures ANOVA with (feedback yes/no) and assessment time (pre/post) with a power of at least 80%, an a priori significance level of .05, and a correlation between assessments of .4, the sample has to include at least *N* = 38 NOT patients in total (IG1 and CG). The incremental effect for feedback with CSTs in comparison with feedback without CSTs was *d =* .31 [48]. We therefore assume a small incremental effect (*d =* .30) for the use of CST in this project. To find this effect in a two-way ANOVA with (feedback yes/no) and assessment time (pre/post) with a power of at least 80%, an a priori significance level of .05, and a correlation between assessments of .4, the total sample has to include *N* = 108 NOT patients in total (IG 1 and IG 2). To make sure, that treatment groups and CST are more comparable with respect to the number of patients, we added for the sample size calculation in the CG half of the NOT patients in IG1/IG2, resulting in at least 27 NOT patients for the CG.

In a previous study the proportion of patients who received at least one alarm signal within the first 8 sessions was approximately 49% [49]. Also, Simon et al. found that 56% of the patients were NOT and therefore received an alarm signal [22]. For our sample size calculation we used a more conservative estimate of 40% of NOT patients, which results in a total sample size of *N* = 338 (CG = 68, IG = 135, IG2 = 135). In order to control for drop-out, we added a puffer of 25% to the required sample size to make sure the power analysis is valid. The described procedure above, results in final sample sizes for each group shown in Table 2.

**Table 2 Tab2:** Intended recruitment and sample size of treatment groups

Treatment	Sample size
Intervention group 1	169
Intervention group 2	169
Control group	85

Three moderators and two mediators of the feedback effect will be investigated in hypotheses 3 and 4 (see also Fig. 1): Moderators: therapists’ attitudes towards feedback, feedback usage and diagnoses; Mediators: Therapists’ awareness for negative developments and treatment length. In order to control for therapist effects, therapists will be modelled as random effects at level two.

Therefore, *Optimal Design Software for Multilevel and Longitudinal Research* (Version 3.01; [50]) was used to determine the minimal effect that can be detected with sufficient power, given the sample size calculation above. Assuming a therapist effect of 5% and k = 50 therapists delivering the treatments to j = 8 patients each, a small effect (d = .2) can be detected with sufficient power (1-β = .8). Thus, given the sample size calculated for the primary hypotheses, the secondary analyses can be conducted with sufficient power using multi-level models (e.g., [51]). Ensuring the stability of the results, all analyses will be checked with Mplus software (e.g., [52]).

Additional Monte Carlo simulations with Mplus (Version 7; [52]) were run to specifically test the mediation models from hypotheses 3 and 4. Assuming again small effects for the direct associations, 10,000 datasets have been simulated with the actual sample size of the study sample. These simulations revealed a sufficient power of 1-β = .874. Thus, given the sample size calculated for the primary hypotheses, the mediation analyses can also be conducted with sufficient statistical power to detect indirect mediation effects adjusting for above described control variables.

Furthermore, the analyses will be controlled for the following potential influencing factors: comorbidity (number of additional diagnoses, additional personality disorders), initial impairment, clinical experience as well as experience with the feedback system.

Finally, the data of the project will have a hierarchical data structure because patients will be nested within therapists. Two-level hierarchical models will be applied to the data to correct for therapist influences [51].

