More studies have been conducted regarding adaptation of ongoing treatments based on routine outcome monitoring and feedback tools. Several international research groups investigated such tools (mostly feedback systems) in randomized controlled trials (RCT). The first three RCTs in that field found that feedback to therapists on patients’ progress was effective in improving patient outcomes, particularly for those patients who showed an increased risk for treatment failure (not on track patients; NOT). The percentage of patients at risk for treatment failure receiving feedback and reaching a reliable or clinical significant improvement was about 14% higher than the rate for the NOT patients without feedback [8–10]. Furthermore, those NOT patients with feedback had an 8% lower deterioration rate than without feedback. Additionally, feedback to therapists of NOT patients led to, on average, longer treatments. However, it led to shorter treatments, on average, for on-track (OT) patients. Those early investigators came to believe that the essential value of feedback systems was to help clinicians become aware of pending treatment failure, something that they could not achieve through clinical intuition [11].

To date, key findings of these original studies have been replicated under different conditions in many investigations and have been reported in four systematic reviews [12–15] and five meta-analyses [16–20]. For example, in a recent review on the effects of feedback Krägeloh and colleagues (2015) report that of the 25 identified studies, 17 showed a significantly positive feedback effect on average or for NOT patients [14]. More detailed information about the size of the effects derive from several meta-analyses [17, 18, 20]. In these studies the significant effect sizes regarding improvement for NOT patients with feedback vs. treatment as usual (TAU) varied between an effect size of g = .22 and g = .53. However, a recent Cochrane report graded the quality of evidence for these effects as low and requests further studies with stronger designs [20]. When clinical support or problem solving tools (CST) were implemented the effect size for NOT patients increased and reached g = .70 [18]. CST’s help to determine the potential cause of deterioration and provide clinical suggestions to adapt or improve treatments at risk for failure.

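### The 108 NOT patients for H2 reproduce only if d = .30 is halved to f in a group-by-time test, so H2 has about 29–39% power, not 80%; H1 carries the same error less firmly.

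*Protocol article*

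**What the plan says.** Under 'Sample size calculation and data analyses' the Protocol article says that "the sample size calculation was done so that the size of these comparisons have sufficient power (1-β = .8", and that "Power analyses for the main hypotheses have been conducted with GPower 3.1 [47". The two main hypotheses are pairwise comparisons among NOT patients.

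- **H1 (IG1 vs CG).** The effect is taken from the literature on feedback against treatment as usual: "The average effect for feedback in NOT patients compared to treatment as usual found in the literature is between *r =* .25 [17". In a two-way ANOVA of group by pre/post, with "an a priori significance level of .05, and a correlation between assessments of .4", the result is "the sample has to include at least *N* = 38 NOT patients in total (IG1 and CG".
- **H2 (IG1 vs IG2).** The published increment for support tools is d = .31, and the plan assumes d = .30. With the same design and inputs, "the total sample has to include *N* = 108 NOT patients in total (IG 1 and IG 2".

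The CG is then set at half an intervention arm, at least 27 NOT patients. With a 40% NOT rate this gives 135, 135 and 68 patients. A 25% addition for drop-out gives 169, 169 and 85, or 423 in total.

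**The concern.** Both effects are contrasts between two treatment conditions. The test they are entered into is a pre/post by group ANOVA. For a plain two-group comparison f = d/2. For a 2 x 2 group-by-time test, f is a quarter of the difference in change. If d was halved and entered as f, the calculation assumed effects twice as large as the text says.

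The figure of 108 drives the arm sizes and the total of 423, and the same section relies on that sample size when it claims adequate power for the secondary analyses. If 108 is too small for d = .30, a null result on H2 would be read as a well-powered negative although the trial had little chance of detecting the increment it assumed.

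**Working it through.** **Inputs**, all from 'Sample size calculation and data analyses': alpha .05, power .80, correlation ρ = .4, two groups, two times (m = 2), r = .25 (H1), d = .30 (H2). Tests are taken as two-sided, and the outcome SD is set to 1.

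**Step 1. Reproduce the plan's figures.** G*Power's formula for the within-between interaction is λ = f²·N·m/(1−ρ), with 1 and N−2 degrees of freedom.

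- H2: f = .30/2 = .15. At N = 108, λ = .0225 × 108 × 2/.6 = 8.10 and power is .805. At N = 106 power is .798. The smallest even N is 108, as stated.
- H1: r = .25 gives d = 2 × .25/√(1 − .0625) = .516, so f = .258. At N = 38, λ = .0667 × 38 × 2/.6 = 8.44 and power is .807. At N = 36 power is .785. The smallest even N is 38, as stated.

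Other routes do not give the pair. The between-factor test needs 248 and 86, one-sided testing gives 84 and 30, and ρ = .5 gives 90 and 32.

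**Step 2. What f means in this test.** Let D be the between-group difference in pre/post change. Once the main effects are removed, the four cells depart by ±D/4, so f = D/4 and D = 4f.

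- H2: D = 4 × .15 = .60 SD, against a stated .30.
- H1: D = 4 × .258 = 1.03 SD, against a stated .516.

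**Step 3. Power at the stated effects.** The variance of a change score is 2(1 − .4) = 1.2. A post-only comparison, or d expressed in change-score SD units, has variance 1.0. Baseline adjustment (ANCOVA) gives 1 − .4² = .84. The standard error is √[v(1/n₁ + 1/n₂)], and power comes from the noncentral t. For H2 on change scores, SE = √(1.2 × 2/54) = .211 and .30/.211 = 1.42. For H1 at 54 vs 27, SE = .258 and .516/.258 = 2.0.

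| Analysis | H2, 54 vs 54 | H1, 54 vs 27 |
|---|---|---|
| Change score / interaction (v = 1.2) | 29% | 51% |
| Post-only, or d in change-score SD (v = 1.0) | 34% | 58% |
| Baseline-adjusted (v = .84) | 39% | 66% |

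At H1's own stated N = 38 (19 vs 19), power on change scores is 29%. Simulation with 20,000 runs agrees: 28.9% for D = .30 and 81% for D = .60 with 54 vs 54, and 50.1% for H1 with 54 vs 27.

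**Step 4. Vary the NOT rate and the retention.** The article cites observed NOT rates of 49% and 56%. 'Full loss' means that the whole drop-out allowance is used, leaving 135, 135 and 68 patients. 'No loss' keeps 169, 169 and 85. Figures are baseline-adjusted.

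| NOT rate, retention | NOT patients: each IG / CG | H2 | H1 |
|---|---|---|---|
| 49%, full loss | 66 / 33 | 46% | 74% |
| 49%, no loss | 83 / 42 | 55% | 84% |
| 56%, full loss | 76 / 38 | 52% | 80% |
| 56%, no loss | 95 / 48 | 61% | 88% |

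On change scores, the last row gives 47% for H2.

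**Step 5. What would be needed, and what is detectable.** For 80% power at d = .30, H2 needs about 422 NOT patients on change scores or 296 with baseline adjustment. With 54 vs 54, the difference detectable at 80% power is .60 SD (change score) or .50 SD (adjusted). With 54 vs 27 it is .73 or .61 SD.

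**The case against.** The article names no G*Power option, so use of the interaction test is inferred from exact reproduction. With two groups and two times, the within-factors option has the same λ and degrees of freedom and gives the same N. This stands as a limit on the wording. It does not rescue the figures, because H2 misses 80% under every analysis in Step 3.

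The lowest pair, 29% and 51%, assumes an unadjusted change score and d in raw SD units. The same section says that analyses will control for initial impairment and use two-level models, which points towards the adjusted figures. How the cited effects were standardised cannot be seen from the article. A range is therefore the right report.

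A reader might infer more than the document supports:

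- **That H1 fails as badly as H2.** It does not. The design exceeds H1's stated 38, and under the article's own higher NOT rates the adjusted power reaches 80–88% in three of the four scenarios above.
- **That 51% is the power of the stated N = 38.** It belongs to 54 vs 27. The figure at 19 vs 19 is 29%.
- **That the 25% buffer is wrong.** It is applied as described (338 × 1.25 = 422.5), and no drop-out rate is given for it to miss.
- **That r = .25 is an error.** The equivalent d of about .52 lies inside the published range, which "varied between an effect size of g = .22 and g = .53". Choosing it is a planning judgement.

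**Conclusion.** The conversion is wrong as written, and the 80% power claimed for H2 at d = .30 is not delivered. At the planned 54 vs 54 NOT patients it is about 29–39%, and the most favourable combination of the article's NOT rates and retention gives 47–61%. H1 has about 51–66% at its planned minimum of 54 vs 27. That shortfall depends on the NOT rate, retention and adjustment, so H2 is the firm defect.

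These figures rest on ρ = .4, two-sided testing at .05 and equal variances, with d taken as a between-group difference. They ignore clustering by therapist. One-sided testing would not repair the design: on change scores at the planned numbers it gives 41% for H2 and 63% for H1.

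**What to change.** 1. Redo the calculation with f = D/4, or with a direct two-sample or ANCOVA formula at correlation .4, and replace the 80% claim with the resulting power for each hypothesis.
2. State the differences detectable at 80% power: for H2 about .60 SD unadjusted or .50 SD baseline-adjusted, and for H1 about .73 or .61 SD.
3. Reconcile the pre/post ANOVA used for sizing with the stated control for initial impairment, by naming the baseline-adjusted model as the main test of H1 and H2.
4. Say in advance that H2 will be interpreted by its confidence interval and not as an 80%-powered test of d = .30.

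The cost is corrected text and a less favourable power statement. No additional patients are required. 'Trial status' reports recruitment still open, with 116 patients in June 2017, so at that date the correction could be made before analysis.
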